Patient benefit was observed by a significant reduction in the amount of X-rays used, with a mean reduction in X-ray fluoroscopy screening time of 35% (*p* = 0.013), a 41% reduction in the amount of iodinated contrast used (*p* = 0.008), and a nearly 1 h reduction in mean operating time (17%, *p* = 0.06) [9]. A further prospective observational cohort study of 119 patients was conducted at Duke University Medical Centre. This reported a mean reduction in procedure time of 17% (*p* = 0.04), with Cydar-EV and a reduction in the number and duration of unexpectedly very long operations [10]. There was also significantly better renal function after the procedure and at 30 days, an indirect metric of the effect of less nephrotoxic contrast agent, and better device positioning. There are no known additional risks of using Cydar EV in comparison to standard treatment. Interruption of the Internet connection during the procedure is possible but rare (< 0.001%).

Demonstrating Cydar-EV improves the outcomes of endovascular surgery at a lower cost for the NHS would be a key demonstration of the potential of digital technology (cloud-computing, big-data, AI) to improve precision and consistency of outcomes for image-guided surgery. It would establish a new concept of data-guided surgery to deliver intelligent planning and outcome analysis, aggregating and learning from existing data to improve the precision, consistency, and transparency of patient outcomes for stakeholders across the NHS: patients, commissioners, hospitals, and clinical teams.

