#### Secondary outcomes

Procedural efficiency:Anaesthetic duration—the time between the beginning of induction and the end of emergence. This will be documented at the time of the procedure by the local research team in minutes.X-ray dose per procedure—fluoroscopy time (FT) (seconds), dose area product (DAP) (Gy.cm2) and cumulative air kerma (CAK) (mGy) should be recorded and documented at the time of the procedure by the local research team. The imaging system used should also be recorded.Contrast dose per procedure—the volume (ml) and concentration (mgI/ml) of the iodinated contrast material used should be recorded by the local research team at the time of the procedure in minutes.Consumable use in the operating theatre for endovascular aortic aneurysm repair—name of device, unit and quantity used, blood products used; details to be completed by nurse in the operating theatre or research nurse at the time of the procedure.Technical success:Proximal and distal seal zone at least 10mm and no evidence of endoleak. This will be documented by the imaging CoreLab team on review of the CT images acquired post-operatively and at 4–12 weeks and at 52 weeks.Patient outcomes:Length of ICU/HDU admission—date and time from admission to date and time of discharge from ICU/HDU; documented by the local research team during the time of admission; ICU and HDU admissions should be documented separatelyPostoperative length of hospital stay—date of procedure to date of discharge from hospital (nights); documented by the local research team during the time of admission.30-day mortality—death of the participant within 30 days of the primary procedure; documented by the local research team; to include date of death (dd/mm/yy) and cause.Re-intervention—any procedure open surgical or endovascular undertaken within 1 year of the primary endovascular aortic aneurysm repair procedure (binary outcome). The type, timing, and number of procedures should also be recorded by the local research team.Adverse events—hospitalisation for any reason within one year of the primary endovascular aortic aneurysm repair; the type of event should be documented and classified as one of the following: musculoskeletal, urological, neurological, ophthalmological, cardiovascular, gastro-intestinal, hepato-pancreato-biliary, dermatological, or other by the local research team, with information captured to understand if linked to re-intervention. For each hospitalisation, the following should also be captured:i.Day case, elective, non-electiveii.Length of hospital stay—date of admission to date of discharge (nights)iii.Length of ICU/HDU admission (if applicable)—date and time from admission to date and time of discharge from ICU/HDUQuality of life—differences in quality of life between intervention and the comparator group and changes in quality of life post-surgery will be measured using data from the patient-completed EQ5D-3L [11] instrument. EQ-5D-3L is a validated measure of health-related quality of life, consisting of a five-dimension health status classification system and a separate visual analogue scale. EQ-5D-3L data will be obtained through face-to-face or telephone interview with the participant at baseline, pre-discharge, 4–12 weeks, and at 12 months follow-up.Cost-effectiveness, as assessed by:Total resource use and costsQuality-adjusted life years (QALYs)—quality of life will be measured by the EQ-5D-3L instrument as described above. In order to be used in the calculation of quality-adjusted life years (QALYs), the EQ-5D-3L dimension scores will be converted to utilities using the relevant value set for England. Quality-adjusted life years (QALYs) gained in both groups, over the time horizon of the trial, will be calculated using the area under the curve method.Incremental cost per QALY

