#### Statistical methods for secondary outcomes

A similar analysis will be undertaken for the secondary outcomes including quality of life scores. Binary outcomes will be compared between arms using logistic regression adjusting for stratification factors. Outcomes will be reported as adjusted differences in means (or median) or odds ratios for continuous and binary data respectively. All tests will be two sided and will be assessed at the 5% significance level. Safety outcomes will be reported as patient proportions and rates within and between arms with 95% confidence intervals using exact methods where appropriate.

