### Composition of the data monitoring committee, its role and reporting structure {21a}

The data monitoring committee (DMC) will be composed of three independent members: a statistician and two clinicians. The DMC is an advisory committee, reporting to the trial steering committee. They will receive a report of recruitment and serious and non-serious adverse events and a summary of accumulated clinical data from the trial statistician and will meet in person or by telephone. The DMC will meet at least annually during the study, approximately 2 weeks prior to the TSC. Members will be independent of the sponsor organisations and of any recruiting study sites. The DMC will work to the DAMOCLES guidance and a DMC charter will be agreed at the first meeting outlining responsibilities, reporting, meeting frequency, documentation, and other matters. The trial statistician will prepare reports for the DMC.

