### Adverse event reporting and harms {22}

Adverse events will be categorised as per the medicines for human use (Clinical Trials) regulations 2004 and amended regulations 2006. Where any adverse event occurs, the relationship with the investigational product will be assessed to determine the relationship and be judged as, definitively, probably, possibly, unlikely, not related, or not assessable. All SAEs, SARs, and SUSARs will be reported immediately (and certainly no later than 24 h) by the investigator to KCTU. The chief investigator will report relevant SAEs to the ethics committee.

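### The only listed adverse-event outcome is all-cause hospitalisation within one year, so it omits complications confined to the index stay, counts planned unrelated admissions, and differs from the term's meaning elsewhere in the protocol

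*Protocol article*

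**What the plan says.** In the protocol article, Outcomes {12}, Secondary outcomes, the adverse-event item reads: "Adverse events—hospitalisation for any reason within one year of the primary endovascular aortic aneurysm repair". The event is classified by body system, "with information captured to understand if linked to re-intervention". The section continues "For each hospitalisation, the following should also be captured" and lists the admission type (day case, elective or non-elective), the nights in hospital, and any ICU or HDU time. The index stay has its own outcome, postoperative length of stay, measured as "date of procedure to date of discharge from hospital (nights"). The Secondary objectives list one adverse-event item, described by category, length of stay and level of care.

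Two other sections use the term differently. Adverse event reporting and harms {22} says: "Where any adverse event occurs, the relationship with the investigational product will be assessed". It also requires serious events to reach the trials unit within 24 hours. The data monitoring committee section {21a} says of its members: "They will receive a report of recruitment and serious and non-serious adverse events".

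The Statistical methods for secondary outcomes section adds: "Safety outcomes will be reported as patient proportions and rates within and between arms with 95% confidence intervals using exact methods where appropriate". It does not list what the safety outcomes are.

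**The concern.** The same term carries two meanings. Under the outcome definition, an adverse event is an admission to hospital. Under the harms and monitoring sections, it is any untoward event, including non-serious ones, which would not normally involve an admission. The two cannot be the same set of events.

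The outcome definition matters because it is the only adverse-event item among the listed objectives and outcomes. Followed as written, the between-arm comparison called adverse events is a comparison of readmissions. A stroke, a kidney injury or a wound infection that arises and is treated before first discharge does not enter it, while a planned day-case admission for something unrelated does.

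This bears on the trial's own rationale. The Background section expects fewer surgical site infections and adverse events, and better renal function from using less contrast. It cites earlier cohort evidence of "significantly better renal function after the procedure and at 30 days". Much of any such benefit, or of a harm, would be expected around the procedure. The data monitoring committee could also see one adverse-event count and the outcome report give another under the same name.

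**Working it through.** The plan states no figure on this point, so there is none to reproduce. The check is mainly a reading of the sections against each other.

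1. **Does the index stay count as a hospitalisation?** The text does not say so either way. If it counted, every treated patient would have an event and the outcome would carry no information. The stay is also measured as a separate outcome. The only workable reading is admission after the index discharge.

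2. **Are planned admissions counted?** Yes. The definition covers admission for any reason, day case and elective are listed types, and nothing excludes them. The link to re-intervention is recorded but is not used to define the event.

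3. **Is index-stay harm recorded elsewhere?** Yes. The harms section covers any adverse event and requires rapid reporting of serious ones. Thirty-day mortality, re-intervention, ICU/HDU time and postoperative stay also reflect part of it.

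4. **Which meaning does the statistical section use?** It does not say. Its safety sentence could cover the hospitalisation outcome, the events under the harms section, or both.

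A numerical illustration shows how the definition behaves. It does not estimate an error in this trial. All event rates are assumptions, because the documents give none. Per-arm n = 153, the evaluable number in Sample size {14}. The half-width of the 95% interval for a difference is 1.96 × √[p₁(1−p₁)/n + p₂(1−p₂)/n].

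- *Outcome as defined*, assuming 30% readmitted in each arm: difference 0, half-width 1.96 × √(2 × 0.21/153) = 10.3 points. The zero is an input, because equal readmission was assumed. At 20% or 40% in both arms the half-width is 9.0 or 11.0.
- *Index-stay complications*, assuming 10% v 20%: difference 10.0, half-width 1.96 × √[(0.09 + 0.16)/153] = 7.9. Assuming 6% v 12%: 6.0 ± 6.4. Assuming 15% v 25%: 10.0 ± 8.9.
- *Any event in either period*, taking the periods as independent, with 10% v 20% in the index stay and 30% readmitted: 1 − 0.90 × 0.70 = 37% v 1 − 0.80 × 0.70 = 44%, giving 7.0 ± 11.0.
- *Dilution by planned admissions*, assuming 10% v 20% unplanned and an independent planned proportion q in each arm. With q = 0: 10.0 ± 7.9. With q = 10%: 1 − 0.90 × 0.90 = 19% v 1 − 0.80 × 0.90 = 28%, giving 9.0 ± 9.4. With q = 20%: 28% v 36%, giving 8.0 ± 10.4.

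The evaluable 153 is not quite the right denominator for safety. Using the protocol's 7.5% loss before the procedure, those who start it would be about 170 × 0.925 = 157 per arm. Half-widths shrink by √(153/157) = 0.987, so 10.3 becomes 10.1 and 7.9 becomes 7.8. Precision barely changes.

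**The case against.** The best case for the plan is that this is largely a labelling matter. Index-stay events are collected under the harms section, serious events are reported within 24 hours, and an unblinded committee sees serious and non-serious events. The safety sentence in the statistical section is not restricted to the hospitalisation item and can be read to cover those events. The detail of event tables is commonly left to an analysis plan, and the full protocol is not shown. The hospitalisation measure has an evident use in the cost analysis, and planned admissions can be separated because admission type is recorded.

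Much of this stands. A reader might infer that the trial fails to collect in-hospital harm or cannot compare it between arms. The documents do not support that, for the reasons just given. A reader might also infer that a death in the index stay goes uncounted, but 30-day mortality is a separate outcome with date and cause. Nor is it right that the device acts only in theatre, so that all harm must be early. The Intervention description includes planning and post-operative review, and the Background notes that positioning error can lead to secondary interventions, which makes a one-year window reasonable.

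The objection does not remove the definition itself. The protocol states what the adverse-event outcome is, and an analysis plan that followed it would report readmissions under that name. Recording admission type permits a split, but the definition does not require one. Leaving open which events the safety sentence covers does not resolve the conflict.

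**Conclusion.** The point holds as a fault in an outcome definition. The only listed adverse-event outcome leaves out complications that begin and resolve in the index stay and includes planned unrelated admissions. The term has a wider meaning in the harms and monitoring sections, and the safety analysis does not say which meaning applies.

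Its size cannot be put as a number for this trial. The illustrative figures rest wholly on assumed rates, on equal readmission between arms and on independence between periods. They show only that a difference confined to the index stay would not register in the outcome as defined, and that planned admissions would dilute a difference in unplanned ones. The exclusion of the index stay is itself an inference, though the only one that leaves the outcome informative. The primary outcome and the sample size are unaffected. It is worth correcting because peri-procedural harm is central to the rationale and the data needed are largely in hand.

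**What to change.** In Secondary outcomes, rename the item *hospital readmission within one year*. Show it in three groups, using the admission type and re-intervention link already recorded: unplanned; planned and linked to the aneurysm or a re-intervention; planned and unrelated. Keep the second group within harm. Counting only unplanned admissions would discard, for example, an elective admission to treat an endoleak.

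In Statistical methods for secondary outcomes, state that the safety outcomes are the serious adverse events reported under the harms section from the start of the procedure. Present them by arm for two periods: the index stay (to first discharge or death), and after discharge to one year. Give patient proportions and a between-arm difference, each with a 95% confidence interval, in all randomised patients who start the procedure. Report non-serious events descriptively only, because site staff and outcome assessors are unblinded and their logging may be uneven.

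The cost is a few extra table rows and a dated clarification made before outcome data are inspected, since recruitment began in May 2022. No new visits are needed, and the readmission data still serve the cost analysis. Some ascertainment risk remains, because event reporting by unblinded staff is less objective than a hospital admission. Limiting the comparison to serious events reduces that risk but does not remove it.

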
### Participant timeline {13}

Figure 4 lays out the trial participant time line of enrolment, intervention, and assessment.

**Fig. 4 Fig4:**
[figure not shown]
Schedule of enrolment, interventions, and assessments of patients in the ARIA trial

### Sample size {14}

There is no known minimum clinically important difference (MCID), and part of the aim of the study is to better characterise the clinical benefit to patients. The study is therefore powered on the basis of a minimum economically meaningful difference. Previous work at Duke [9] reported data on the primary outcome, procedure time, and found a mean difference of 22.5 min (17%) for patients with an abdominal aortic aneurysm treated with Cydar-EV 109.6 (34.2) and standard 2D fluoroscopy imaging 132.1 (69.2) minutes. This is a meaningful difference in the NHS context as this time reduction per case would allow four rather than three EVAR procedures to be performed per day, which is a productivity increase of 33% at the same capacity. The SD for procedure time increases with the mean and so we have assumed a *t*-test for ratio of means 1.2 (fold change), assuming a lognormal distribution for the calculations. Therefore, a sample size of 153 patients per arm with a 1:1 allocation ratio (2 × 153 = 306) would give us 90% power at the 2-sided 5% significance level to detect this difference (PASS 15 Power Analysis and Sample Size Software (2017)). Since our primary outcome measure requires the procedure to be completed, we need to inflate the sample size for possible: (i) loss post randomisation, pre-procedure (est. 7.5%), and (ii) on-table death and cross-overs (where surgeons may use the intervention in a control arm patient and additional assistance is required to complete the operation) (est. 2.5%). These inflate the sample size to 170 per arm. The final randomisation target is therefore 2 × 170 = 340. The Duke data also showed using Cydar-EV in TAAA showed larger reductions in operating time than for AAA. We have powered on the more conservative difference since the relative proportions of AAA/TAAA patients anticipated in our proposed trial is unknown.

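### The 90% power at 153 per arm assumes equal relative spread in both arms, which the plan's own quoted SDs contradict; on those figures an unadjusted log-scale test has about 67% power

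*Protocol article*

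**What the plan says.** Sample size {14} in the protocol article takes its effect from an earlier cohort of patients with abdominal aneurysm. Mean (SD) procedure times there were "treated with Cydar-EV 109.6 (34.2) and standard 2D fluoroscopy imaging 132.1 (69.2) minutes", a difference of 22.5 min or 17%. Its reason for working with a ratio is that spread is expected to grow along with average procedure time. The test is specified as one "for ratio of means 1.2 (fold change), assuming a lognormal distribution for the calculations". It concludes that 153 patients per arm "would give us 90% power at the 2-sided 5% significance level to detect this difference". A 10% allowance for losses raises this to 170 per arm, 340 in all. No CV is printed, and the section does not say whether the 1.2 is a ratio of arithmetic or of geometric means.

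The section on statistical methods for the primary outcome plans a normalising transformation if one is needed and can be found, then linear regression adjusted for the minimisation factors, with quantile regression as the fallback.

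**The concern.** A t-test on lognormal data compares mean log times, so it tests the ratio of geometric means. That ratio equals the ratio of arithmetic means only when both arms have the same CV. The quoted means differ by a factor of 1.2 but the quoted SDs by a factor of 2.0, so the cohort does not show a common CV. Part of the 22.5 min then reflects a shorter right tail with Cydar-EV, which the log scale largely discounts. The background section describes the same pattern in that cohort: "a reduction in the number and duration of unexpectedly very long operations".

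At stake is how a null result would be read. A log-scale analysis that found no difference could be presented as a well-powered negative when, on the quoted figures, the chance of missing the cited effect was nearer one in three than one in ten.

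**Working it through.** **Inputs** (all from Sample size {14}): Cydar-EV mean 109.6, SD 34.2; standard imaging mean 132.1, SD 69.2; ratio 1.2; 153 per arm; two-sided 5%; 90% power.

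**1. Reproducing the plan's figure.** For a lognormal variable, log-scale variance = ln(1 + CV²). With CV 0.52 in both arms the variance is ln(1.2704) = 0.2393 (log-SD 0.489), and the effect is ln 1.2 = 0.1823.
- Normal approximation: n = 2 × (1.960 + 1.282)² × 0.2393 / 0.1823² = 151.3, so 152 per arm.
- Noncentral t: 153 per arm, power 90.1%. This matches the plan.
- With the unrounded control CV, 69.2/132.1 = 0.524, the t-based answer is 155, and power at 153 is 89.8%.
- The other common-CV choices tried do not give 153: the Cydar-EV CV gives 60, the mean of the two CVs 103, their root mean square 109, and pooled SD over overall mean 119. A comparison of arithmetic means with both quoted SDs gives 124.
- Inflation: 153/0.90 = 170, as stated.

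The common CV of 0.52 is therefore inferred from the reproduction and from the remark that the SD grows with the mean; the plan does not state it.

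**2. What the quoted figures imply.**
- CVs: 34.2/109.6 = 0.312 and 69.2/132.1 = 0.524.
- Log-scale variances: 0.0929 and 0.2425.
- Geometric means, mean × exp(−variance/2): 104.6 and 117.0 min, ratio 1.118.
- Log difference: ln(132.1/109.6) − (0.2425 − 0.0929)/2 = 0.1867 − 0.0748 = 0.1119, against the 0.1823 used in step 1.

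**3. Power of the unadjusted log-scale test at 153 per arm.**
- SE = √((0.2425 + 0.0929)/153) = 0.0468; z = 0.1119/0.0468 = 2.39.
- Power = Φ(2.39 − 1.96) = 66.7%. The noncentral t gives 66.4%, and 40,000 simulated trials give 66.9%.
- For 90%: n = (1.960 + 1.282)² × 0.3354 / 0.1119², about 282 per arm before losses.

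**4. How far this moves.**
- Cydar-EV CV, with the means and the control CV as quoted: 0.31 gives 67%, 0.35 gives 72%, 0.40 gives 79%, 0.45 gives 85%, 0.50 gives 89%, 0.524 gives 91%.
- Covariate adjustment: if covariates explain 30% of log-scale variance, z = 2.39/√0.70 = 2.86 and power is about 81%. About 46% would have to be explained to reach 90%.
- Shape, same means and SDs (simulation): lognormal above a minimum procedure time of 20 to 60 min gives about 77% to 95%; a gamma distribution gives about 42% to 44%.
- 1.2 read as a geometric-mean ratio, with the quoted CVs: z = 0.1823/0.0468 = 3.89, power about 97%.
- Arithmetic means: SE = √((69.2² + 34.2²)/153) = 6.24; z = 22.5/6.24 = 3.61, power 95.0% (simulation 96.5%).

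**The case against.** The strongest reply is that nothing was miscalculated. The plan adopts a lognormal model in which SD grows with the mean, and under that model with a common CV of 0.52 the design has 90% power. It powers on a minimum economically meaningful difference and does not claim to replicate the cohort's full distribution. Carrying the larger CV into both arms is also cautious as regards variance. All of this stands, so the fault is not an arithmetic error.

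The caution about variance does not make the result conservative overall, however. Equalising the CVs also removes the 0.0748 reduction in the log effect, and that outweighs the gain from the smaller variance.

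A reader might go further and infer that the trial truly has 67% power. The documents do not support this:
- They give means and SDs only. The medians are derived from an assumed shape, and other shapes with the same means and SDs move the figure widely in both directions.
- The SDs come from patients with abdominal aneurysm in an observational cohort; the trial also takes thoraco-abdominal and emergency cases.
- The primary analysis is fixed neither to the log scale nor to an unadjusted test. The adjustment gain is unknown because no share of explained variance is given.
- If 1.2 was meant as a geometric-mean ratio, the quoted SDs give more than 90%. Against that reading, the only figures offered are arithmetic means, whose ratio is 1.205, and the argument from procedures per day rests on total minutes.

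**Conclusion.** Wrong as written: the power statement rests on an unstated assumption that the figures in the same section contradict. The plan claims "90% power at the 2-sided 5% significance level to detect this difference", where the difference just described is 22.5 min (17%) between arithmetic means. If the arms have the quoted means and SDs and are lognormal, an unadjusted log-scale t-test at 153 per arm has about 67% power for that difference. Of these inputs, the two-parameter lognormal shape and the absence of covariate gain are the least secure. The 90% is valid only as a conditional statement, for a 1.2-fold geometric-mean ratio with a common CV of 0.52.

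Two further inferences do not follow. The sample size need not be raised, since 153 per arm gives about 95% power for arithmetic means on the same figures. Nor does this point show that the primary analysis must move to arithmetic means: that is a choice of estimand, which a power calculation cannot settle.

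**What to change.** Keep 340 patients and reword Sample size {14}:
- State the CV used and whether 1.2 is a ratio of arithmetic or of geometric means.
- Make the power conditional, for example: 90% power for a 1.2-fold geometric-mean ratio with a common CV of 0.52; if the arms have the quoted means and SDs and are lognormal, the unadjusted log-scale test has about 67% power for the 22.5 min difference, and a comparison of arithmetic means about 95%.
- Show the range over the Cydar-EV CV (67% at 0.31 to 91% at 0.524), and note that shape and covariate adjustment also move it.

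The cost is a rewording, with no extra patients and no change to trial conduct. The drawback is a less favourable stated power if the primary analysis is done on the log scale.

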### Outcomes {12}

#### Primary outcome

Primary efficacy parameter of the study is procedure duration, measured as the time between insertion of the first wire (after percutaneous access achieved, if applicable) at the beginning of the endovascular procedure to the last frame of the completion angiogram. This will be recorded (in minutes) at the time of the procedure by the local research team.

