#### Statistical methods for primary outcome

As the primary outcome is procedure duration and we envisage 7.5% loss of patients between randomisation and procedure, the primary analysis will be a per-protocol (PP) analysis based on procedure time. The primary analysis will be conducted after completion of first follow-up (at 4–12 weeks) which will include procedure time as well as the secondary outcome data available at this time. Sensitivity analysis with multiple imputation for missing data will also be conducted alongside the per-protocol analysis. No significance tests will be performed for baseline comparison. The primary outcome measure is likely to have a skewed distribution and therefore if necessary and possible the data will be normalised using an appropriate transformation. The data will then be analysed using linear regression techniques with stratification (minimisation) factors included as covariates. If a suitable transformation cannot be found, the data will be analysed using quantile regression to allow us to include the addition of the stratification factors as covariates.

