### Methods in analysis to handle protocol non-adherence and any statistical methods to handle missing data {20c}

Compliance with intervention will be recorded in the source data worksheets and transcribed to the EDC system. Reasons for non-compliance would include device failure, surgeon error, or failure to communicate correct randomisation allocation to the surgeon. The patient could only impact compliance if they express a wish to withdraw between randomisation and surgical procedure. Missingness will be reported and reasons for missingness explored. Although a low percentage of missing data is anticipated, a sensitivity analysis of the primary outcome will be undertaken in order to assess the impact of the exclusion of participants with missing intraoperative data in the primary analysis. In this view of the sample size, a modelling approach will be taken rather than multiple imputation.

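### Procedure time is undefined when no completion angiogram is reached, so started but uncompleted repairs leave the primary analysis, and the missing-data plan gives them no rule of their own

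*Protocol article*

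**What the plan says.** Under Primary outcome, procedure duration runs from insertion of the first wire "to the last frame of the completion angiogram". No other end time is defined.

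Under Sample size {14}, the article states that "our primary outcome measure requires the procedure to be completed" and inflates 153 per arm to 170 for two kinds of loss. The first is loss between randomisation and procedure (7.5%). The second is on-table death and cross-over, estimated together at 2.5%.

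Under Statistical methods for primary outcome, the primary analysis is per-protocol, and "Sensitivity analysis with multiple imputation for missing data will also be conducted alongside the per-protocol analysis".

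Section {20c} promises a sensitivity analysis of "the impact of the exclusion of participants with missing intraoperative data in the primary analysis", but says that modelling will be used in preference to multiple imputation. It also says that missingness will be reported and its reasons explored.

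Conversion to open repair and abandonment of a started procedure are not mentioned in any of these sections.

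**The concern.** A duration that was not written down and a duration that never came to exist are different things. After an on-table death there is no time to completion to recover. The plan puts both under missing data and removes both from the primary comparison.

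The second kind is a post-randomisation event that image guidance might affect. The article's background expects the device to improve procedural success and reduce adverse events, and it cites earlier data with fewer unexpectedly very long operations. The trial is open label, so a decision to stop or convert is made with the allocation known. Emergency and complex thoraco-abdominal repairs are eligible.

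If uncompleted procedures are more frequent in one arm and tend to be long, removing them makes that arm look faster. The comparison then becomes one of time among completers, and a larger sample does not change that. If the time at which the attempt ended is not recorded, no later analysis can bring these patients back.

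**Working it through.** **1. The plan's own figure.** The inputs come from Sample size {14}: control "standard 2D fluoroscopy imaging 132.1 (69.2) minutes", a t-test "for ratio of means 1.2 (fold change), assuming a lognormal distribution for the calculations", and "90% power at the 2-sided 5% significance level".

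- Control CV = 69.2/132.1 = 0.524.
- Log-scale SD = √ln(1 + 0.524²) = √0.2425 = 0.4924.
- n per arm = 2 × 0.2425 × (1.960 + 1.282)² / (ln 1.2)² = 2 × 0.2425 × 10.51 / 0.03324 ≈ 153.3, so 154. The noncentral t gives 155.
- Power at the stated 153 is 0.899.
- Inflation: 153/0.90 = 170.

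The stated 153 and 170 are reproduced to within two patients.

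**2. How many patients.** The 2.5% allowance is 170 × 0.025 = 4.25 per arm, or 8.5 in total. It includes cross-overs, who can have a completion time, so the share with no outcome is below 2.5% on the protocol's estimate. The allowance names neither conversion nor abandonment.

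**3. Worst-case effect of one-sided loss.** Assume that the lost fraction q lies in one arm only and consists of that arm's longest cases. Removing the top q of a normal distribution lowers its mean by σ·φ(z₁₋q)/(1 − q). The standard error of the difference is 0.4924 × √(2/153) = 0.0563.

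- q = 2.5%: 0.4924 × 0.05845/0.975 = 0.0295.
- q = 5%: 0.4924 × 0.10314/0.95 = 0.0535.
- q = 1.25%: 0.4924 × 0.03236/0.9875 = 0.0161.

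Type I error is Φ(−1.96 + shift/SE) + Φ(−1.96 − shift/SE). Power, when the loss is in control, is Φ((0.1823 − shift)/SE − 1.96), where 0.1823 = ln 1.2.

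| Loss, one arm | Fall in that arm's geometric mean | Share of ln 1.2 | Type I error | Power if the loss is in control |
|---|---|---|---|---|
| none | 0 | 0 | 5.0% | 89.9% |
| 1.25% | 1.6% | 9% | 5.9% | 83.9% |
| 2.5% | 2.9% | 16% | 8.2% | 77.5% |
| 5% | 5.2% | 29% | 15.8% | 62.9% |

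**4. Milder case.** With 2.5% lost in control and 1.25% in the device arm, again the longest cases, the net shift is 0.0295 − 0.0161 = 0.0134. Shift/SE is 0.24, type I error 5.6% and power 85%.

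**5. Simulation check.** This used 157 per arm (170 × 0.925), with the longest cases removed and a t-test on the log scale. One-sided loss gave type I error of 8–9% at 2.5% and about 17% at 5%. Power with the loss in control was 80% and 67%, somewhat higher than in the table because n is larger and trimming shrinks the observed SD.

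A 2.5% loss in both arms left the estimated ratio at 1.00 under no effect and 1.20 under the target effect, so there was no bias. The t-test rejected in 6.5% of null runs, against 4.7% without loss, because its standard error ignores the trimming.

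**The case against.** - **Part of the remedy is already planned.** Section {20c} commits to a sensitivity analysis of this exclusion and to exploring reasons for missingness, and a CONSORT diagram will show exclusions. This stands, and it is why the fix extends that analysis instead of inventing one. It does not close the gap, because no section gives an uncompleted procedure its own rule or an end time.
- **Imputation.** A reader might infer that these patients will be imputed as ordinary missing values, with durations typical of completed cases. The documents do not support that. One section plans multiple imputation and another rejects it, neither says which patients it would cover, and the analysis plan is not shown. What can be documented is the contradiction and the lack of any distinction.
- **The 2.5% is not a failure rate.** This stands. It includes cross-overs, and the background gives overall mortality of only 1.7% for endovascular repair. The 5% case has no source in the documents and is an illustration.
- **The error rates are corner values.** This also stands. An on-table death or early abandonment may be short, and nothing in the documents shows that losses will fall in one arm. The need for written consent also keeps out patients who lack capacity, and probably some of the least stable.
- **Failures are seen elsewhere.** Thirty-day mortality, technical success, re-intervention and anaesthetic duration are secondary outcomes. This helps interpretation but does not correct the primary comparison.
- **Censoring has its own assumption.** Right-censoring treats a failed case as if it would have continued like others of the same duration, which may be untrue, especially after death. This limits the proposed model to a sensitivity analysis.

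**Conclusion.** The concern holds in a limited form. The outcome definition and the per-protocol analysis together exclude started but uncompleted procedures, and sample-size inflation does not address that selection. For on-table deaths the article says so; for conversions and abandoned repairs it follows from the definition.

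Whether bias results depends on a difference between arms that the documents cannot predict. The upper end is about 8% type I error or 78% power at a 2.5% loss, and about 16% or 63% at 5%. Both need all losses in one arm and all from its longest cases, with a log SD of 0.492 and 153 per arm. At half the 2.5% figure, type I error is about 6% and power 84%. These figures bound the problem; they do not forecast this trial's error rate.

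The change should be made because it is cheap and because an end time that is not recorded may not be recoverable later.

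**What to change.** 1. For every procedure in which the first wire was inserted, record the clock time at which the endovascular attempt ended, whether or not a completion angiogram was taken.
2. Report the number of uncompleted procedures by arm, with the reason, beside the primary result.
3. Reconcile the two missing-data statements. State separately how an unrecorded time and an undefined completion time are handled.
4. Make the sensitivity analysis in section {20c} cover all started procedures. Enter uncompleted ones as right-censored at elapsed time in a log-normal regression with the same covariates as the primary model, and state that this censoring may be informative.

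The primary analysis is unchanged and so is the target. If the whole 2.5% group were retained, 153/0.925 = 165.4, or 166 per arm, would be enough, and 170 are planned. The cost is one data field and one additional model.
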